## What is the proposed frequency of analyses?

There will not be a planned interim analysis in the present study given that it is a pilot study with a small anticipated sample size (n=88).

## Are there any planned subgroup analyses?

There are no subgroup analyses planned as this is a pilot RCT.^54^

# TRIAL MANAGEMENT

## What are the arrangements for day-to-day management of the trial?

Patient recruitment will occur through individual surgeon clinics as well as the clinic of one of the principal investigators ([name]), should extra visits be required. Data will be captured via a combination of anthropometric measurements (i.e., height, weight), patient completed paper/electronic forms and questionnaires, and electronic medical records. De-identified data will be recorded in a firewall, password protected database. All study records will be kept on an encrypted and password-protected computer that will be kept with our lead biostatistician ([name]). Only authorized study personnel will have access to these data.

**Describe the trial steering committee and if relevant the data safety and monitoring committee.**

[name] will be the principal investigator for the present RCT, and part of his responsibilities will be to oversee day-to-day trial management. He will be supported by a steering committee, as well as research assistants and biostatisticians. The steering committee will be involved through study inception until study completion. The steering committee will oversee design, data collection, data management, interpretation of the data, and manuscript generation. This committee will hold the primary responsibility for publication of the trial results. It will be comprised of both clinical and methodologic experts; specifically, the principal investigators, national leaders, and individuals with knowledge in specific areas or in clinical trial methods. [name] will meet with the steering committee at least once during the planning, recruitment, and close-out phases of the trial, and at any other time point as deemed necessary by the principal investigators.

To provide more frequent oversight of the study, a subset of the steering committee will constitute the operations committee. This committee will be composed of a select group of investigators chosen for their specific expertise and experience. The operations committee is ultimately responsible for all decisions regarding the design and conduct of the trial. Outcome adjudication committees and statistical analysis sub-committees blinded to treatment allocation will be formed and oversee data collection, extraction, and analysis. An equity, diversity, and inclusion (EDI) sub-committee will be formed to ensure that all relevant EDI aspects of this trial are identified and managed.

An independent Data Monitoring Committee (DMC) will be established and lead by an independent physician to monitor and adjudicate adverse events throughout the trial. Occurrence of all serious adverse events will be collected, where applicable, in keeping with laws and regulations governing the study site. All serious adverse events will be fully documented on appropriate case report forms outlining onset, duration, treatment required, outcome, and action taken. These data will be iteratively evaluated by the DMC and should there be cause for concern for patient safety moving forward at any point in the trial, they will consult with the principal investigators to discuss premature termination of the study.

# BUDGET

| **Budget Details** | | | |
| --- | --- | --- | --- |
| 1. **Personnel** | **Hours** | **Salary** | **TOTAL** |
| McMaster Payroll Research Assistant 1: UNIFOR5555, Grade 6, Step 2, 35% Fringe Benefits | 20h/wk  52 wks  1,040 h | $33.75/h | $35,100.00 |
| McMaster Payroll Research Assistant 2: UNIFOR5555, Grade 6, Step 2, 35% Fringe Benefits | 10h/wk  52 wks  520 h | $33.75/h | $17,550.00 |
| Research Clerk (salary + 4% in-lieu of vacation) | 5h/wk  52 wks  260 h | $15.00/h | $4,056.00 |
| McMaster Biostatistician (35% Fringe Benefits) | 3h/wk  52 wks  156 h  (0.075 FTE) | Annual: $81,000  0.075 FTE | $6,075.00 |
| **Total Personnel** | | | **$62,781.00** |
| 1. **Supplies** | | | |
| Optifast® 900 program | | | $13,200.00 |
| Patient parking for non-routine clinical visits | | | $3,520.00 |
| Office supplies and printing | | | $1,000.00 |
| **Total Supplies** | | | **$17,720.00** |
| 1. **Services** | | | |
| Data Entry Services | | | $3,500.00 |
| Randomization Software | | | $2,500.00 |
| **Total Services** | | | **$6,000.00** |
| 1. **Knowledge Translation** | | | |
| Open Access Publication | | | $3,500.00 |
| Conference Presentation | | | $4,000.00 |
| **Total Knowledge Translation** | | | **$7,500.00** |
| **TOTAL AMOUNT** | | | **$94,001.00** |

## Budget justification

The total budget for this project is $94,001.00

Personnel

A Research Assistant is required to provide support for this project over the course of one year. The Research Assistant will be responsible for preparing study documents, aiding in Research Ethics Board applications, consenting patients, data collection, and liaising with the various trial stakeholders. The hourly wage of a Research Assistant at McMaster University is $25.00 +35% fringe benefits, which equates to $33.75 per hour. It is anticipated that they will work, on average, 20 hours per week for a total of 1 year on this project (20 hours/week x 52 weeks = 1,040 hours). As such, their compensation for the present project will be $33.75 x 1,040 hours = $31,500.00.

In addition, a second Research Assistant will be required to provide support for this project over the course of one year at the same cost as above, but at half the number of weekly hours. We will rely on this Research Assistant to obtain anthropometric measures for patients at their pre-very low energy diet (VLED) visit, post-VLED visit, and postoperative visit ($33.75 x 520 hours = $17,550.00).

A research clerk, paid at minimum wage ($15.00/h) for a temporary casual employee with an additional 4% wage in-lieu of vacation, will be employed to aid with input of paper data collection forms into electronic format to allow for data analysis. It is anticipated that they will work an average of 5 hours per week over the course of a year (5 hours/week x 52 weeks = 260 hours). As such, their compensation for the present project will be $15.00 x 260 hours + (4% x total) = ­$4,056.00.

The biostatistician is a staff statistician in the Department of Oncology at McMaster University. Under the supervision of the one of the study investigators, [name], they will be responsible for creating a randomization list, importing and formatting data for SAS/STATA software, cleaning the data, and completing the final analysis. It is estimated their services will be required for an average of 3 hours per week over the course of a year (0.075 full time equivalents (FTEs)). Their annual salary is $81,000. As such, the estimated cost for a year for their biostatistical services is 0.075 FTE x $81,000.00 = $6,075.00.

Supplies

All enrolled patients will adhere to the Optifast® 900 or Medimeal® program for three weeks. The weekly cost of the Optifast® 900 or Medimeal® program is approximately $100.00. The cost of the three-week program will be $300.00 ($100.00/wk x 3 weeks = $300.00) per patient and we will continue enrollment until 88 patients, half of which will be in the intervention arm (44 patients x $300.00/patient = $13,200.00).

Patients will be required to make to non-clinically scheduled in person visits for the purposes of the study. Following consent and enrollment, they will require baseline measures of height and weight, as well as symptoms, prior to commencing the study intervention/placebo. They will also require an in-person one-month postoperative follow-up for the purposes of the study that may not align with their scheduled follow up with their respective surgeon. Parking at St. Joseph’s Healthcare Hamilton or Hamilton Health Sciences is approximately $20.00 per visit. Given that each patient will have two visits (2 days x 88 patients x $20.00/patient/day) we will budget $3,520.00.

Patients will be provided with printed study information booklets, Optifast® 900 handouts, diet diaries, and a copy of their informed consent information. The SF-36 and symptom questionnaires will also be administered via paper forms. As such, $1,000.00 is anticipated for printing and associated office supply costs.

Services

Database preparation and entry of all study data will be organized under the supervision of the one of the study investigators, [name], Estimated cost is $3,500.00.

The randomization service provided by randomization.net costs $2,500.00.

Knowledge Translation

The final version of the manuscript from this project will be published in an Open Access journal in order to increase accessibility and aid in knowledge dissemination. The mean publishing fee for large Open Access journals (e.g., BioMed Central, PLoS) ranges from approximately $2,000.00 to $4,000.^55^

The findings generated from this pilot RCT will be presented at an international (e.g., Digestive Disease Week) and a national (e.g., Canadian Surgery Forum) conference. Registration, travel, and accommodations for each is approximately $2,000.00 ($2,000.00/conference x 2 conferences = $4,000.00.

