# THE PROPOSED TRIAL

## What is the proposed trial design?

The proposed trial will be a multi-center, surgeon, outcome assessor, and data-analyst blinded, parallel pilot RCT.

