## What are the proposed practical arrangements for allocating participants to trial groups?

Patient recruitment will occur at Hamilton Health Sciences, St. Joseph’s Healthcare Hamilton, and Kingston Health Sciences. All surgeons who perform elective non-bariatric surgery at these sites will be made aware of the study via workshops and internal communications. Patients will be identified by the surgeons, their administrative assistants, and/or study investigators at the time of referral, at the time of their initial preoperative consultation, or some time following their initial preoperative consultation. Surgeons and/or other clinicians within a patient’s circle of care will introduce the study to participants at the time of their preoperative visits or sometime thereafter. Patients may also reach out directly to study investigators via the contact information provided on the study poster should they choose. Patients meeting inclusion criteria based on a review of their electronic medical record, which will only be accessed by persons within the circle of care or researchers that have obtained permission from the patient, will have their contact information (i.e., email and phone number) recorded and provided to designated research personnel at the time of their initial surgical consultation in clinic. This email contact information will then be passed into a novel automated clinical trials platform developed by Phelix AI©. This platform will automatically send an electronic version of the written informed consent document to the patient as well as a link to schedule an appointment in the following 1-2 days with the research team to discuss the informed consent document via telephone. If the Phelix AI© platform identifies that the patient does not have an accessible email address, this will trigger a notification to the research team and prompt them to call the patient by telephone. At the time of initial contact between the study personnel and patient, the study will be introduced, eligibility will be confirmed. Patients will be provided with the opportunity to ask questions about the previously circulated ICF, and if they have yet to review the document, they will review the document in its entirety with the research team at the time of the telephone contact. If, at the end of this process, patients are understanding of the material risks and benefits of participation, and wish to be enrolled in the study, they will sign the ICF and subsequently be randomized to one of the two arms in this parallel RCT. Following ascertainment of written informed consent, patients will be randomized via a web-based randomization system (randomization.net) in a 1:1 fashion to receive either standard of care plus preoperative VLED or standard of care alone. Randomization will be according to variable block sizes of four and six and will be stratified according to centre.

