## What are the proposed methods for protecting against sources of bias?

This trial will be randomized with variable block sizes which will protect against selection bias. In addition, surgeons, outcome assessors, and data analysts will be blinded to treatment allocation in order to reduce the risk of selection bias, measurement bias, and detection bias. Blinding of outcome assessors will be achieved via the establishment of an Independent Outcomes Adjudication committee. Given the nature of the intervention, we will be unable to blind patients which may raise the possibility of recall bias during reporting of symptom and quality of life questionnaires at the one-month follow-up. We will aim for completeness of follow-up in all randomized patients which will protect against imbalance of prognosis afforded by our randomization strategy. Lastly, we will limit crossovers and co-interventions through thorough documentation of the preoperative period to avoid contamination and the resultant impact on effect size estimates.

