## What are the proposed types of analyses?

Descriptive statistics (means, medians, standard deviations, interquartile ranges, proportions) will be used to characterize the study sample. The outcomes of the pilot study will be descriptive in nature and will focus on feasibility. Binary outcomes will be described using proportions with corresponding 95% CIs estimated using the Wilson Score method. Differences in continuous outcomes will be described using the difference in means with corresponding 95% CIs. Considering the feasibility nature of this pilot study, and following the 2010 CONSORT statement, we will not assess statistical significance for outcomes.^53^ We will calculate aggregated measures for 30-day postoperative morbidity to compare this to the tentative power calculation in the “Full Trial Power Calculation” associated document, to ensure an accurate power calculation is performed for the fully powered RCT. The proposed data analysis plan for the full RCT is reported in the “Full Trial Statistical Analysis Plan” associated document. Data will be analyzed using STATA statistical software (StataCorp version 15; College Station, TX). All data analysis will be completed by a blinded statistician.

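### The protocol declares the data analyst blinded, yet gives one budgeted biostatistician both the randomization list and the final analysis, and states no safeguard between them

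*Protocol*

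**What the plan says.** Three sections of the protocol claim that the analysis is blinded.

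- **Trial design:** "The proposed trial will be a multi-center, surgeon, outcome assessor, and data-analyst blinded, parallel pilot RCT".
- **Protection against bias:** "surgeons, outcome assessors, and data analysts will be blinded to treatment allocation". This is offered as a safeguard, and the same section concedes that patients cannot be blinded.
- **Types of analyses:** "All data analysis will be completed by a blinded statistician".

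The Budget justification, under Personnel, lists the duties of the staff biostatistician: "they will be responsible for creating a randomization list, importing and formatting data for SAS/STATA software, cleaning the data, and completing the final analysis".

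On how allocation is delivered, the section on allocating participants says "patients will be randomized via a web-based randomization system (randomization.net) in a 1:1 fashion" and adds "Randomization will be according to variable block sizes of four and six and will be stratified according to centre". The Services part of the budget text adds "The randomization service provided by randomization.net costs $2,500.00". None of these statements says who generates the list or who keeps it.

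**The concern.** A statistician who builds an allocation list with real arm labels, and later cleans and analyses the same trial's data, is not blinded in the usual sense. The duties in the budget text and the blinding claims elsewhere therefore pull against each other.

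Three things are at stake. First, judgements made during cleaning (which values to query, recode or set aside) could be made by someone able to see allocation. Second, the between-arm summaries of clinical and safety outcomes would come from that same person. Third, the trial would be reported as analyst-blinded although its own protocol describes duties that do not fit the label. Because patients are unblinded, the protocol relies more than usual on blinding its surgeons, assessors and analysts.

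**Working it through.** No figure in the protocol bears on this point, so the check compares the text section by section.

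**Step 1: are the blinded statistician and the list-maker the same role?** The section on types of analyses does not name its statistician, but it covers all data analysis. The Budget justification gives the final analysis to the staff biostatistician. The final analysis is part of all analysis, so whoever does it must be blinded under one section and is the list-maker under the other. The personnel table agrees: it has one biostatistician line (3 hours a week × 52 weeks = 156 hours, 0.075 FTE) and no second statistician who could be unblinded. The identity is an inference, but a direct one.

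**Step 2: does the web service separate the roles?** It could, if it generated the sequence and kept it hidden. The protocol says that patients are randomized through the service and that the service is paid for. It does not say that the service creates or withholds the list, and the budget text says the biostatistician creates it. The protocol thus leaves the source and custody of the list unsettled.

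**Step 3: what would it take to unblind the analyst?** Two things: a list carrying the true arm labels, and a way to match list positions to participants. Randomization is stratified by centre, so the order of randomization within each centre would supply the match. If the list held only dummy codes, with the labels attached inside the web system, its author would stay blind. The protocol mentions neither dummy codes nor a separate holder. The correct conclusion is that blinding is contradicted as written and not assured. It does not follow that blinding has certainly failed.

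**Step 4: which results could be affected?**

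| Result | Between-arm contrast? | Exposed? |
|---|---|---|
| Randomization percentage | No | Hardly |
| Recruitment rate | No | Hardly |
| Intervention compliance | No, intervention arm only | Hardly; a single-arm mean by definition |
| Follow-up completion | No | Hardly; defined in the protocol and recorded by a research assistant on a standard form |
| Differences in means for continuous outcomes, with 95% CIs | Yes | Yes, through cleaning and analysis |
| Adverse events and 30-day morbidity by arm | Yes, if tabulated by arm | Partly; a blinded committee adjudicates outcomes |

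**Step 5: is there another route to the allocation?** Yes, and it is independent of who makes the list. Compliance is defined only for participants randomized to the diet, and control patients are told to leave the diary blank. Any participant-level diary field therefore shows the arm to whoever handles it. This does not add to the contradiction in Step 1, but it does mean that relabelling the arms would not by itself keep the analyst blind.

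**The case against.** The strongest reply is that a budget paragraph is not a delegation log. The trial management text refers to biostatisticians in the plural, to a lead biostatistician who keeps the study records, and to statistical analysis sub-committees blinded to allocation. The contents also list a section on the roles of the applicants. It was not in the text available here and might name a list-holder. Allocation is issued by a web system and the recorded data are de-identified. Masked codes and staged data releases are normally left to a statistical analysis plan.

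Part of this stands. The absence of coding and data-release detail is not a fault in a protocol, and the single-person reading is inferred. The reply does not remove the conflict, however. The budget paragraph is the only itemized account of the statistician's duties in the available text, and it joins two tasks that the blinding claim requires to be kept apart. The sub-committee text restates the blinding without saying who holds the list.

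A reader might go further and infer three things that the documents do not support:

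- **That the analyst's blinding is lost for all 88 records.** This would need a labelled list that can be linked to participants, and the protocol does not say that the list is labelled.
- **That the pilot fails to test a blinded workflow it was meant to pilot.** The five feasibility objectives are recruitment, compliance, follow-up, the site network and safety. Analyst blinding is not among them.
- **That the analyst could decide which visits count as complete.** The protocol defines completion and has a research assistant record it.

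**Conclusion.** The point holds as an internal contradiction: a stated design property conflicts with stated duties, and no safeguard in the available text reconciles them. The conclusion rests on two assumptions. One is that the final analysis in the budget text falls within the blinded analysis described elsewhere. The other is that no list-holder is named in the section that could not be read.

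The size is modest, and any bias cannot be quantified from the protocol. No statistical significance will be assessed, and the go/no-go criteria do not depend on comparing arms. The exposure is confined to data cleaning, the between-arm clinical and safety summaries, and whether the trial can fairly be described as data-analyst blinded. Severity is minor to moderate. The protocol should be corrected, but the feasibility decisions are not threatened.

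**What to change.** 1. State in the allocation section that randomization.net, or a named role with no part in data cleaning or analysis, generates and holds the list.
2. Remove list creation from the biostatistician's duties in the Budget justification.
3. State that the analyst works with masked arm codes. Supply the intervention-only diary and compliance fields as a separate file, released once between-arm cleaning and tables are fixed. The detail can sit in the analysis plan.
4. If the roles cannot be separated, withdraw the analyst-blinding claim from the sections on trial design, protection against bias and types of analyses, and bring the committee description into line.

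The change is best made before the list is produced, because a person who has seen a labelled list cannot be blinded afterwards. If the list already exists, record who made it and whether it carried real labels.

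The cost is small: a few sentences and a split data export. The randomization service is already budgeted at $2,500. Sample size, visits and outcomes are unaffected.
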